## Abstract

**Background:**

Heart failure patients with stable angina, acute coronary syndromes and valvular heart disease may benefit from revascularisation and/or valve surgery. However, the mortality rate is increased- 5-30%. Biventricular pacing using temporary epicardial wires after surgery is a potential mechanism to improve cardiac function and clinical endpoints.

**Method/design:**

A multi-centred, prospective, randomised, single-blinded, intervention-control trial of temporary biventricular pacing versus standard pacing. Patients with ischaemic cardiomyopathy, valvular heart disease or both, an ejection fraction ≤ 35% and a conventional indication for cardiac surgery will be recruited from 2 cardiac centres. Baseline investigations will include: an electrocardiogram to confirm sinus rhythm and measure QRS duration; echocardiogram to evaluate left ventricular function and markers of mechanical dyssynchrony; dobutamine echocardiogram for viability and blood tests for renal function and biomarkers of myocardial injury- troponin T and brain naturetic peptide. Blood tests will be repeated at 18, 48 and 72 hours. The principal exclusions will be subjects with permanent atrial arrhythmias, permanent pacemakers, infective endocarditis or end-stage renal disease.

After surgery, temporary pacing wires will be attached to the postero-lateral wall of the left ventricle, the right atrium and right ventricle and connected to a triple chamber temporary pacemaker. Subjects will be randomised to receive either temporary biventricular pacing or standard pacing (atrial inhibited pacing or atrial-synchronous right ventricular pacing) for 48 hours.

The primary endpoint will be the duration of level 3 care. In brief, this is the requirement for invasive ventilation, multi-organ support or more than one inotrope/vasoconstrictor. Haemodynamic studies will be performed at baseline, 6, 18 and 24 hours after surgery using a pulmonary arterial catheter. Measurements will be taken in the following pacing modes: atrial inhibited; right ventricular only; atrial synchronous-right ventricular; atrial synchronous-left ventricular and biventricular pacing. Optimisation of the atrioventricular and interventricular delay will be performed in the biventricular pacing group at 18 hours. The effect of biventricular pacing on myocardial injury, post operative arrhythmias and renal function will also be quantified.

**Trial Registration:**

ClinicalTrials.gov: NCT01027299

## Background

The prevalence of heart failure is increasing throughout the industrialised world. Approximately 2-3% of the general population are diagnosed with heart failure [1] and the primary aetiology is coronary artery disease. A retrospective analysis of heart failure trials has identified at least 62% of subjects have coronary disease [2]. The total financial cost to the National Health Service is approximately £ 563 million per annum in 2006-7[3].

Modern medical therapy has substantial reduced both morbidity and mortality after a myocardial infarction. ACE inhibitors [4,5], beta blockers [6-8] and aldosterone antagonists [9,10] modulate the renin-angiotensin-aldosterone axis and neurohormonal cascade which reduces major adverse events. These medications arrest the cascade of progressive ventricular remodelling and dilatation observed in heart failure. Further ventricular remodelling can be achieved with biventricular (BiV) pacing through the reversal of electro-mechanical dyssynchrony. The reduction in ventricular volumes correlates to a reduction in heart failure events, arrhythmias and death [11,12].

Heart failure patients with stable angina and a significant burden of coronary artery disease may benefit from surgical revascularisation. However, the risk of surgery is increased and mortality rates range from 5-30% [13]. There is limited randomised control data on surgical revascularisation in subjects with severe left ventricular (LV) systolic dysfunction- ejection fraction ≤ 35%. The landmark trials of surgical revascularisation in the 1970 excluded subjects with significant LV dysfunction [14,15].

The Coronary-Artery Bypass Surgery in Patients with LV Dysfunction (STICH) trial was specifically designed to address this issue and compared optimal medical therapy to surgical revascularisation, in subjects with severe LV systolic impairment [16]. The primary endpoint of all cause mortality was not significant between the 2 groups at 56 months follow-up (41% medical v 36% surgical; p = 0.12). However, the secondary endpoint of death or cardiovascular hospitalisation was less likely in the surgical group (68% v 58%; p < 0.001).

A sub-study of the STICH trial (n = 601) also investigated the prognostic value of myocardial viability in patients with severe LV systolic impairment [17]. Viability was assessed using single-photon emission computer tomography or dobutamine echo. After adjustment for baseline variables there was no significant association between viability and mortality (p = 0.21). Neither was there a significant interaction between viability status and treatment assignment with respect to mortality (p = 0.53). However, previous meta-analysis of viability (n = 3088) reported a 79.6% reduction in annual mortality with revascularisation versus medical therapy when viable myocardium was detected (16% v 3.2%, p < 0.0001) [18]. There was no advantage of revascularisation in non-viable myocardium.

The ESC guidelines on myocardial revascularisation 2010 [13] recommend surgical revascularisation in chronic heart failure (ejection fraction ≤ 35%) in the following circumstances- Table 1:

**Table 1 T1:** Indications for surgical revascularisation in heart failure.

Indication	Class	Level
CABG is recommended for:	I	B
• Significant left main stenosis		
• Left main equivalent		
• Proximal LAD stenosis, with 2 or 3 vessel disease		

LV aneurysmectomy during CABG is indicated in patients with a large LV aneurysm.	I	C

CABG should be considered in the presence of viable myocardium irrespective of LV end-systolic volumes.	IIa	B

CABG with ventricular reconstruction may be considered in patients with scarred LAD territory.	IIb	B

Revascularisation in the absence of myocardial viability is not recommended.	III	B

In addition, heart failure patients with unstable coronary syndromes and valvular heart disease are potential candidates for cardiac surgery. In view of the increased pre-operative risk of surgery, interest has focused on techniques including temporary BiV pacing, to optimise cardiac function and outcome in the post operative period.

BiV pacing can be performed after cardiac surgery via temporary epicardial wires attached to the right atrium, right and left ventricle. Through a mechanism of reversing electro-mechanical dyssynchrony, BiV pacing can augment stroke volume and cardiac output without increasing myocardial oxygen demand. An acute haemodynamic response has been observed in previous studies during implantation of permanent BiV pacemakers - Table 2.

**Table 2 T2:** Trials of acute haemodynamic response to biventricular pacing.

Investigator	Study title	Sample	Result
Breithardt [26], 2003.	Acute effects of CRT on MR in systolic heart failure.	N = 24 EF ≤ 30% LBBB	Reduction in MR and improvement in dP/dT with BiV, p < 0.0001.

Leclerq [27], 1998.	Acute haemodynamic effects of BiV in patients with end-stage heart failure.	N = 18 NYHA ≥ 3 QRS ≥ 120	Increase in cardiac index BiV pacing v AAI, p < 0.001.

Aurrichio [28], 1999.	Effect of pacing chamber and AV delay on acute systolic function of paced patients with heart failure.	N = 27 NYHA ≥ 3 LBBB	Improvement in LV dP/dT with BiV pacing v DDD(RV) pacing, p < 0.01.

Kass [29], 1999.	Improved LV mechanics from acute VDD pacing in patients with DCM and conduction delay.	N = 18 QRS ≥ 120	Improvement in LV dP/dT with BiV pacing v AAI, p < 0.05.

These studies were conducted on subjects after optimising medical therapy including ACE inhibitors and beta blockers. Temporary BiV pacing after cardiac surgery has additional considerations. The haemodynamic performance of this technique maybe affected in the presence of inotropes and vasopressors, anaesthetic agents, intra-aortic balloon counter-pulsation, positive pressure ventilation and myocardial injury after circulatory arrest. In addition, ACE inhibitors are frequently discontinued prior to surgery because of post operative hypotension and renal dysfunction [19].

Previous trials of temporary BiV pacing after cardiac surgery have produced mixed results- Table 3.

**Table 3 T3:** Acute BiV pacing studies after cardiac surgery.

Investigator	Study title	Sample	Result
Pokushalov [20], 2010.	CABG with CRT in patients with ischaemic heart failure and dyssynchrony.	N = 178 EF ≤ 35% QRS > 120	Reduced mortality with CRT, p = 0.006, reduced LOS and improved CI at 48 hours, p < 0.001.

Eberhardt [30], 2009.	BiV pacing after CABG in patients with reduced LV function.	N = 94 EF ≤ 40%	No significant difference between BiV and other pacing modes on haemodynamics or LOS.

Hanke [24], 2009.	BiV pacing after cardiopulmonary bypass in patients with reduced LV function.	N = 21 EF < 35% QRS > 120	BiV superior to DDD(RV) pacing but not DDD(LV) or AAI pacing.

Evonich [31], 2008.	Temporary BiV pacing in cardiac patients with severely reduced LV function.	N = 40 EF ≤ 30%	No significant change in LOS or haemodynamic function with BiV.

Hamad [32], 2009.	Acute haemodynamic effect of CRT in patients with poor LV function during surgery.	N = 11 QRS > 130 EF ≤ 35%	Optimised (VV) BIV pacing improved haemodynamics (p = 0.03) v RV pacing.

Muehlschlegel [33], 2008.	Temporary BiV pacing after CABG in patients with reduced ejection fraction.	N = 10 EF < 50% QRS > 120	Significant improvement in cardiac output with BiV v DDD(RV or LV).

Dzemali [34], 2008.	Impact of different pacing modes on LV function following CABG.	N = 80 EF ≤ 35%	Patients with dilated LV (mean 65 v 52mm) more likely to respond to BiV, p < 0.001.

The largest trial in this series (Pokushalov et al [20]) enrolled subjects with baseline dyssynchrony. This included a QRS duration > 120 msec or the echo criteria for dyssynchrony used in the CARE-HF trial [21]. In addition, the effect of BiV pacing was not measured in subjects with an intra-aortic balloon pump. Therefore, additional studies to assess the clinical and haemodynamic effects of BiV pacing in all subjects in sinus rhythm with severe LV systolic impairment, ejection fraction (EF) ≤ 35% irrespective of baseline dyssynchrony are indicated. This includes haemodynamic studies of BiV pacing in subjects who require intra-aortic balloon counter-pulsation and further evaluation of atrioventricular (AV) and interventricular (VV) optimisation.

## Methods/Design

### Hypothesis

• Post operative biventricular pacing may improve acute haemodynamic function after surgery by reversal of electro-mechanical dyssynchrony.

• Temporary BiV pacing may reduce the requirements for inotropic support, ventilation and renal replacement therapy and hence the duration of level 3 care.

• Optimisation of BiV pacing intervals may provide additional haemodynamic benefit compared to nominal settings.

### Study design

A multi-centred, prospective, randomised, single-blinded, intervention-control trial of patients with severely impaired LV systolic function (EF ≤ 35%) undergoing cardiac surgery for revascularisation, valve surgery or both. Inclusion and exclusion criteria are detailed in Table 4.

**Table 4 T4:** Inclusion and exclusion criteria.

Inclusion criteria	Exclusion criteria
Age > 18 years	Permanent pacemaker or defibrillator

Sinus rhythm	Infective endocarditis

Surgical revascularisation, valve surgery or both	Hypertrophic cardiomyopathy

	Off pump cardiac surgery

	Permanent atrial arrhythmia

	Renal failure (dialysis dependent)

	Emergency revascularisation.

The trial was approved by the 'Research and Development' departments, at the University Hospital of Wales, Cardiff (09/CAD/4628-sponsor) and Morriston Hospital, Swansea, UK (S10CardS961). The trial has been approved by the Dyfred Powys Research Ethics Committee-09/WMW01/27. The trial will be conducted in accordance with the 'Declaration of Helsinki' and all subjects will provide written consent. This trial is registered with clinicaltrials.gov NCT01027299.

### Pre-operation

Patients will be invited to participate in the trial if they are awaiting cardiac surgery. This includes elective patients and in-house referrals scheduled for revascularisation, valve surgery or both. Subjects with a recent history of an acute coronary syndrome or episode of decompensated heart failure (< 30 days) will be included. However, unstable subjects with medically refractory angina and/or pulmonary oedema requiring emergency surgery will be excluded from the trial.

After enrolment an ECG will be performed to confirm sinus rhythm and measure QRS duration and a transthoracic echocardiogram to measure ejection fraction using the Simpson's bi-plane method of discs. A detailed echo study will be performed (GE, Vivid 7, Horten, Norway), to evaluate LV systolic and diastolic function, valve function and cardiac dyssynchrony- Table 5. Subjects with EF > 35% will exit the trial.

**Table 5 T5:** Echo protocol.

Echo window	Modality	Measurement
Parasternal long axis	MMode	LV internal dimensions
		LV wall thickness
		Septum to lateral wall delay
	Colour flow	Mitral regurgitation

Parasternal short axis	PW doppler	RVOT- pulmonary pre-ejection interval (PPEI)
	CW doppler	PA acceleration time

Apical 4 chamber	2D	LA and RA area
		LVEDV and LVESV
	MMode	Long axis displacement- RV lateral/LV septal and
		lateral walls
	Colour flow	Mitral regurgitation
	PW doppler	Mitral inflow
		LVOT- aortic pre-ejection interval (APEI)
		IVRT
	MVI	Medial and lateral E'
		Basal segments- peak velocity.

Apical 2 chamber	2D	LVEDV and LVESV
	MVI	Basal segments- peak velocity.

Apical 3 chamber	MVI	Basal segments- peak velocity.

Echo measurements of dyssynchrony included:

• Interventricular mechanical delay (= APEI-PPEI)

• Atrio-ventricular delay (APEI)

• Time-delay to peak systolic velocity in the basal segments of the septal and lateral wall using myocardial velocity imaging (MVI) Q analysis.

A repeat transthoracic echo will be performed after discharge from the cardiac intensive care unit (CITU) between day 3 and 5 post surgery.

Baseline blood tests will be sent to measure:

• Full blood count (Haemoglobin, haematocrit and mean cell volume)

• Creatinine (eGFR calculation)

• TnT: Troponin T

• BNP: Brain naturetic peptide

• NGAL: Neutrophil gelatinase associated lipocalin- renal injury

Blood samples will be taken at baseline, 18 hours, 48 hours and 72 hours after admission to CITU.

An assessment of myocardial viability using dobutamine stress echo (GE, Vivid 7, Horten, Norway) will be considered for each patient. Each case will be discussed with the cardiac surgeon before this test. Principal exclusions will be a recent acute coronary syndrome or episode of decompensated heart failure, valvular heart disease, prior viability assessment or physician preference. Viability assessment will be performed by an experienced operator with ECG and blood pressure monitoring. Dobutamine will be initially infused at a rate of 5 microg/kg/min and increased in steps to 10, 20, 30 and 40 micrograms every 3 minutes. Atropine 0.25 mg will be added as a bolus at intervals of 1 minute up to a total dose of 1 mg. The maximum target heart rate = [(220-age) × 0.85]. Viability will be defined as 5 or more segments with abnormal resting function but manifesting contractile reserve during dobutamine testing [17].

### Randomisation

Randomisation into 2 groups will be performed after induction of anaesthesia using commercially available software to minimise for confounding variables -Table 6. Group 1 will be assigned to BiV pacing and group 2 to standard pacing. Standard pacing will be atrial inhibited pacing (AAI) unless right ventricular pacing is required, then atrial-synchronous right ventricular pacing (DDD-RV) is indicated. The intended duration of pacing will be 48 hours, but could be modified by the attending physician.

**Table 6 T6:** Variables considered at the time of randomisation.

Parameter	Reference	
LV size	≤ 60 mm	> 60 mm

QRS duration	≤ 120 msec	> 120 msec

Euroscore	≤ 10	> 10

Intra-aortic balloon pump	No	Yes

Valve surgery	No	Yes

Ejection fraction	≤ 20%	> 20%

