### Endpoints

The primary endpoint of the trial is the duration of level 3 care [22] required after cardiac surgery. Level 3 care is defined as the duration of invasive mechanical ventilation or multiple organ support or multiple inotropes/single inotrope and intra-aortic balloon pump. The majority of patients would reach the primary endpoint after extubation and then once weaned down to a single inotrope. In the cases where inotropes are restarted, the endpoint is taken to be the final transition from level 3 to level 2 care before discharge from the intensive care unit.

Secondary endpoints are:

• Cardiac index at 18 hours (AAI v BiV).

• Duration and total dose of inotropes/intra aortic balloon counter-pulsation.

• Renal function and requirement for haemofiltration.

• Arrhythmia after surgery until hospital discharge.

• Change in brain naturetic peptide, troponin T and neutrophil gelatinase associated lipocalin.

• Myocardial infarction, re-intubation or re-sternotomy.

• 30 day all cause mortality.

Subjects will complete the trial 30 days after the operation.

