### Statistical Analysis

No previous studies have investigated the effect of BiV pacing on the duration of level 3 care after cardiac surgery; previous studies have reported the total duration of CITU stay.

Pokushalov et al [20] reported an average CITU stay of 3.9 ± 0.6 days in the subjects after cardiac surgery, compared with 2.5 ± 0.5 days in subjects who had BiV pacing after cardiac surgery - a 36% reduction. We anticipate that the duration of level 3 care will be shorter than the duration of CITU stay, perhaps with less variance, but we have used these mean values and standard deviations for our power calculation.

Using the standard formula described by Campbell and Matchin [23]:

$$\text{Sample}\;\text{size}=\frac{2\times {\left({\text{Z}}_{1\alpha }+{\text{Z}}_{2\beta }\right)}^{2}\times \sigma^{2}}{\delta^{2}}$$

σ = standard deviation of the population

δ = anticipated benefit from the intervention

(Z_1α _+ Z_2β_) = normal distribution of function

(1-β) = 80% and α = 5%.

From standard tables (Z_1α _+ Z_2β_) ^2 ^= 7.85

$$\text{Sample}\;\text{size}=\frac{2\times \left(7.85\right)\times 0.6^{2}}{{\left(0.15\times 3.9\right)}^{2}}=\frac{5.652}{0.342}=16.5$$

In order to demonstrate a 15% reduction in the duration of level 3 care, with power 80% and with p < 0.05 for a two-sided test, the estimated total sample size required is 34 subjects.

For haemodynamic comparison of paired data at 18 hours to compare BiV pacing to standard (AAI) pacing, Hanke et al [24] observed a cardiac index of 2.7 ± 0.6 L/min/ml^2 ^in the standard pacing group. Allowing a 0.3 L/min/ml^2 ^(11%) improvement in cardiac index with BiV pacing, significance 5% and power 80%, a sample size of 32 subjects would be required.

Considering both of these previous studies, the minimum number of subjects who will be recruited and randomised into this study, will be 34; allowing for a 1/3 drop-out rate, the minimum number to be recruited will be 45. In the 2 cardiac surgical centres in which this study will be performed the proportions of all patients undergoing cardiac surgery who have impaired LV function and sinus rhythm, and who would therefore be eligible for the study are 2% and 8% (approximately 65 patients in a total of 1414 operations per year); this study should therefore be feasible within a maximum of 2 years.

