Data obtained for the primary endpoint and haemodynamic studies will be analysed for normality using the Kolmogorov-Smirnov test. Normally distributed variables will be analysed using unpaired or paired Student's T tests respectively. Non-parametric data will be analysed using the Mann-Whitney U or Kruskal-Wallis test. If continuous variables are not matched between intervention and control groups at baseline, inter-group comparisons will be made using an analysis of covariance with adjustments made for baseline differences. Changes in proportions for categorical data will be analysed with the Chi-square test or Fisher's exact test.

Analysis will be intention-to-treat and a p-value of < 0.05 will be considered statistically significant.

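### Centre is neither a listed minimisation factor nor a term in the stated primary test of this two-centre trial; a prespecified centre term would protect a 34-patient comparison at almost no cost

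*Protocol article*

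**What the plan says.** The abstract states that patients "will be recruited from 2 cardiac centres". The Randomisation section says: "Randomisation into 2 groups will be performed after induction of anaesthesia using commercially available software to minimise for confounding variables". It points to Table 6 ("Variables considered at the time of randomisation"), which names LV size, QRS duration, Euroscore, intra-aortic balloon pump, valve surgery and ejection fraction. Centre does not appear, and no stratification by centre is mentioned.

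Under Endpoints, the primary endpoint is the duration of level 3 care, and "The majority of patients would reach the primary endpoint after extubation and then once weaned down to a single inotrope".

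Under Statistical Analysis: "Normally distributed variables will be analysed using unpaired or paired Student's T tests respectively". Non-normal data go to the Mann-Whitney U or Kruskal-Wallis test. The one adjustment provided is an analysis of covariance, which applies "If continuous variables are not matched between intervention and control groups at baseline". Centre is categorical, so this condition does not reach it.

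**The concern.** Centre is a routine balancing factor and model term in a multicentre trial because unmeasured differences in practice travel with it. They could matter here: the endpoint stops when clinicians extubate and reduce inotropes. The article standardises anaesthesia and bypass technique and sets haemodynamic targets, but gives no shared extubation or weaning rule.

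Two things are at stake if the centres differ in mean level 3 duration. In a trial of 34, the arms can by chance hold different centre mixes, and an unadjusted estimate absorbs that difference. Even with balanced arms, the difference between centres stays in the residual and widens the confidence interval.

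**Working it through.** **Inputs from the article (Statistical Analysis).** SD 0.6 days; target effect 0.15 × 3.9 = 0.585 days; two-sided 5%; 80% power; "the estimated total sample size required is 34 subjects". Equal allocation is not stated but is implied by rounding 16.5 per group up to 17 and doubling.

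**Plan's own figure.** 2 × 7.85 × 0.6² / 0.585² = 5.652 / 0.342 = 16.5 per group, so 17 per arm and 34 in total. This reproduces. At 17 per arm, power is 81% by the normal approximation and 78.7% for the t test itself.

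**Centre split.** The eligible proportions are 2% and 8%, giving about 65 patients in 1414 operations a year. Solving 0.02x + 0.08(1414 − x) = 65 gives x = 802 operations at one centre and 612 at the other. That is about 16 and 49 eligible patients, or roughly 25:75. I assume that recruitment follows this split.

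**Chance imbalance.** Treat allocation as independent of centre; minimising on Table 6 balances centre only so far as centre correlates with those factors. With each patient coming from the smaller centre with probability 0.25 and 17 per arm:
- arms differ by 4 or more smaller-centre patients: 16%
- arms differ by 5 or more: 7%

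With a fixed smaller-centre count, the chance of a difference of 4 or more is 8.5% for 7 patients, 22.5% for 8 and 11.8% for 9. The figure jumps because the difference must be even when the count is even and odd when it is odd. Since 25% of 34 is 8.5, no single fixed count is the natural one, and I take 16% as the summary.

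**Shift in the estimate.** Let g be the between-centre gap in mean duration. The documents do not give g; all values are assumptions. The SD of the difference in centre share between arms is √(2 × 0.25 × 0.75 / 17) = 0.1485. The 95% range of the shift is ±1.96 × 0.1485 × g:

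| g (days) | 95% range of shift (days) | share of 0.585 |
|---|---|---|
| 0.3 | ±0.09 | 15% |
| 0.6 | ±0.17 | 30% |
| 1.0 | ±0.29 | 50% |

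Averaged over allocations the shift is zero, and simulation (40,000 runs) keeps the unadjusted type I error at 5%. Among runs with an imbalance of 5 or more, it is about 7% at g = 0.3 and 12% at g = 0.6.

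**Power if 0.6 is the within-centre SD.** Without a centre term the SD is √(0.36 + 0.1875 g²), where 0.1875 = 0.25 × 0.75:

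| g (days) | SD without centre term | t-test power | power with centre term (simulated) |
|---|---|---|---|
| 0 | 0.600 | 79% | 77% |
| 0.3 | 0.614 | 77% | 77% |
| 0.6 | 0.654 | 72% | 77% |
| 1.0 | 0.740 | 61% | 77% |

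The centre term costs about 1.5 points when the centres do not differ.

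**Power if 0.6 is the total SD.** At g = 0.6 the within-centre SD is √(0.36 − 0.1875 × 0.36) = 0.541. By the normal approximation, adjusted power is about 88% against 81% unadjusted. Planned power is kept; a gain is left unused.

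**The case against.** The strongest case against is that the size rests on a centre gap that the article never gives. Gaps of 0.6 and 1 day are 1.0 and 1.7 planning SDs, and both exceed the 0.585-day target effect. At 0.3 days the loss is under 2 points. This stands, and the results are conditional for that reason.

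Three stronger readings are tempting, and the document does not support them.

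- **The omission biases the trial.** A reader might infer a systematic bias. There is none: over allocations the estimate is unbiased and the type I error is held. What remains is conditional on a chance imbalance, a risk shared by any prognostic factor left out of a small trial.
- **The 2% and 8% show that the centres manage patients differently.** They are shares of surgical patients with impaired LV function and sinus rhythm. They describe case mix or referral, and say nothing about weaning or level 3 duration among patients who all have EF ≤ 35%. Dependence on local practice is inferred from the endpoint definition and the absence of a stated weaning rule.
- **The trial is underpowered because of centre.** This follows only if 0.6 is a within-centre SD. It is taken from CITU stay in another study, and the article itself expects level 3 duration to vary perhaps less.

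It is also fair to say that an unseen analysis plan could add a centre term, and that the article may not describe how the software was run at each site. The first does not dispose of the point, because the article names the primary test and the only adjustment to it. The second does limit the allocation half.

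**Conclusion.** The point holds in a limited form. As stated, the plan handles centre neither in allocation nor in the primary test, and the conditional covariance analysis does not fill the gap. If the centres differ by about 0.3 days the consequence is small. If they differ by 0.6 days or more, it is material: a chance shift of up to about 30% of the target effect at 0.6 days and, if 0.6 is the within-centre SD, about 7 points of t-test power (79% to 72%). These figures assume a 25:75 split, 17 per arm, allocation independent of centre, and a gap that the document does not supply. No figure in the article is wrong on this point. The case for change is that the protection is nearly free.

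**What to change.** **Main change.** Before any unblinded analysis, prespecify centre as a fixed term in the primary analysis: a linear model of level 3 duration on treatment and centre or, if the data are not normal, a van Elteren test stratified by centre. This is available for every patient, whenever recruited. The cost is one degree of freedom and about 1.5 points of power if the centres do not differ.

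**Secondary change.** Add centre to the Table 6 factors for the remaining allocations or, if minimisation already runs separately in each centre, say so in one sentence. The reach is modest: Trial status reports 31 recruited, against stated minimums of 34 randomised and 45 recruited, so roughly 3 to 14 patients remain. The cost is one setting in the software.
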